## Flow chart of needs analysis of physical functioning and QoL of PD persons

Ethical approval will be obtained from UKMMC and the contact information will be collected from medical rehabilitation of UKMMC and MPDA. Participants will be contacted via WhatsApp based on their contact information obtained from the registry either from UKMMC or MPDA. Ethical approval will be obtained from UKMMC and letter of collaboration from MPDA as attached in appendix 3. Patient information sheet (appendix 4) and informed consent sheet (appendix 5) will be distributed to all participants who fit the eligibility criteria. Once eligible participant provide the informed consent, questionnaire containing three sections as explained in outcome measurement section will be provided via WhatsApp. Data will be analysed descriptively using SPSS and reported as frequency, percentage, mean, standard deviation. Flow of the needs analysis is described in Figure 1.

Report writing

Data analysis

Data collection using part II of MDS-UPDRS and PDQ-39

Provide patient information sheet and informed consent

Contact and screen participants for eligibility

Obtaining ethical approval

Figure 2 Flow chart of needs analysis study

## Outcome measurement tools

Data will be collected using outcome measurement tool as attached in appendix 6. The questionnaire will be created using Google form and be circulated via online platform such as WhatsApp to be answered by the participants (person with Parkinson’s disease). The questionnaire consists of three sections, namely demographic data, Movement Disorder Society-Unified Parkinson’s Disease Rating Scale (MDS-UPDRS) Part II: Motor Aspects of Experiences of Daily Living (M-EDL) and 39-Item Parkinson’s disease Questionnaire (PDQ- 39). Demographic data section contains questions regarding age, gender, race, marital status, working status, duration of Parkinson’s disease, stage of Parkinson’s disease and care taker.

Part II in MDS-UPDRS assess the motor of experiences of daily living. It consists of 13 self- reported items which are speech, saliva and drooling, chewing and swallowing, eating tasks, dressing, hygiene, handwriting, doing hobbies and other activities, turning in bed, tremor, getting out of bed, a car, or a deep chair, walking and balance and freezing. All items are scored on a scale from 0: normal, 1: slight, 2: mild, 3: moderate and 4: severe. MDS-UPDRS has high internal consistency with Cronbach’s Alpha 0.79 – 0.93 (Goetz et al. 2008). It shows comparative fit index > 0.90 for each part thus, the sum score for each part can be reported separately (Goetz et al. 2008).

The PDQ-39 assess quality of life. It consists of 8 dimensions which are mobility (10 items), activities of daily living (6 items), emotional well-being (6 items), stigma (4 items), social support (3 items), cognitions (4 items), communication (3 items) and bodily discomfort (3 items). Rating are made based on Likert scale from never, occasionally, sometimes, often and always. PDQ-39 shows acceptable internal consistency with Cronbach’s Alpha 0.59 –

0.94 and test-retest reliability with intra-class correlation coefficient 0.67 – 0.87 (Tan et al. 2004).

## (8) Statistical tool

Statistical Analysis Statistical Package for Social Sciences (SPSS) will be used and variables namely the level of physical functioning and QoL will be analyzed descriptively, presenting in mean and standard deviation.

## FGD

1. **Study design**

FGD utilizes qualitative approach using semi structured interview in FGD. Main feature of FGD in phase I, analysis is the interactive discussion of module development by a group of all participants (family caregivers) and a team of facilitators in a setting. This is the most popular and traditional focus group discussion format (O. Nyumba et al. 2018). Findings from the FGD along with literature review findings will be used in finalizing the training program content prior to its development using the ADDIE model.

## Target population

Family-caregiver of persons with PD in stage I and II.

## Sample population

Family-caregiver of persons with PD in stage I and II, registered with the MPDA or referred to the Medical Rehabilitation Services Department of UKMMC.

## Inclusion and exclusion criteria of participants

Table 2 Eligibility criteria of participants for FGD

| **Inclusion criteria** | **Exclusion criteria** |
| --- | --- |
| Main family caregiver who lives with the PD patient in stage I-II Hoehn and Yahr (HY) scale | 1. Providing part-time caregiving due to availability of maid/helper |
|  | 2. Presence of clinically diagnosed depression with a cutoff point of  ≥16 in Center for Epidemiologic  Studies Depression Scale (CES-D). |
|  | 3. Presence of mild cognitive impairment or dementia with a cutoff point of ≤26 in Montreal Cognitive  Assessment (MoCA). |

All instruments used for screening the eligibility of participants (family caregivers) are attached in Appendix 2.

## Sample size and number of FGD

Two groups of FGD consisting of a maximum of 12 participants (family caregivers) each will be conducted to gather their needs related to training and ideas and opinions in designing and developing a relevant structured, multi-component family caregiver-training program for people with PD. There will be a minimum of 2 session of FGD, until data saturation is obtained (O. Nyumba et al. 2018).

## Duration, Mode and Venue of FGD

Duration of FGD will be between one to two hours (O. Nyumba et al. 2018). The mode of session; either virtually of face to face will be determined by the preference of the participants. Virtual session will be held using Microsoft Teams and the session will be recorded. If participants agree for face to face session, FGD will be held in the physiotherapy department of UKMMC.

## Flowchart of FGD

Figure 3 illustrates the flow of FGD. Participants will be recruited via purposive sampling from Medical Rehabilitation Services Department of UKMMC and from MPDA based on the eligibility criteria as mentioned earlier. A minimum of two sessions of FGD will be conducted to discuss and its procedure will be briefed verbally and using a written information sheet as in Appendix 7. Participants will be asked to sign an informed consent form prior to the FGD as attached in Appendix 5. Arrangements on date and time for FGD will be based on the convenience of all participants. A quiet location will be determined at the Physiotherapy Unit at UKMMC if face to face session is preferred for the FGD or alternatively virtual session using Microsoft Teams will be arranged. The group will be asked to discuss issues pertaining the needs and care of PD patients according to a list of pre-prepared and piloted open-ended questions, then to suggest the content of the family training program. The researchers will play the role of a moderator and guide the focus group members on the discussion throughout the session. Views from each group member will be tape-recorded (face to face session) or recorded if it is a virtual session by another researcher who is also responsible to take field notes. To prevent fatigue, the maximum duration of each FGD will be limited to 2 hours and more sessions will be decided based on data saturation (O. Nyumba et al. 2018).

Adopt and pilot test to validate the questions developed for FGD

Screening participants for eligibility

Providing information sheet and obtaining informed consent

Participants gathered either virtually or face to face session

First FGD session: Introduction of the session by the facilitator

Moderator A begins semi strutured interview

Moderator B will be taking field notes

Transcription of data

2nd session of FGD as similar process as before

Decide data saturation or conduct more session of FGD

Thematic analysis

Report writing and using the data for Phase II

Figure 3 Flow chart of FGD

## Statistical analysis

Data analysis will be done according to the principles of qualitative research. All recorded data will be transcribed verbatim and thematic analysis will be performed. Triangulations in data analysis will be ensured by including an independent researcher and respondents’ validation will be done prior to finalizing the FGD findings. The steps of performing thematic analysis is as described below (Maguire & Delahunt, 2017):

- 1. Data familiarization
     1. Data transcriptions and multiple reading (read and re-read) of the transcripts
     2. Writing early impression upon reading
  2. Generation of initial code
     1. Meaningful and systematic data organization to highlight important pattern
     2. Inductive analysis will be used for initial coding
     3. Step 1 of inductive analysis involves two types of approaches in vivo coding and structural coding. Participants’ own word will be used to generate code in in vivo coding and in structural coding, sections of the data will be coded to address the questions from the open – ended survey questions.
     4. Step 2 involves line by line coding to add on more details to the initial coding.
  3. Theme searching
     1. Preliminary primary themes and subthemes will be sorted from relevant coded data extracts
  4. Theme reviewing
     1. Review each data set mapped to the appropriate theme
     2. May involve appraisal, modification and development of the themes
  5. Theme defining
     1. Themes will be finalized
  6. Report writing

## PHASE II

Phase II of the study involves the designing and development phase of ADDIE model. The design phase involves planning on strategy to achieve goal set in analysis stage and resource identification to develop the module (Muruganantham, 2015). While, the development phase begins with construction and development of the module and its instrument plus instructions using media software and documentation (Muruganantham, 2015).

## Module designing

Two researchers will be involved in the early draft of module and the storyboard based on the phase I FGD report and literature review. Researchers will also meet a group of subject experts for discussion on their respective components for their module. Team of experts in this study consist of neurologist, nurses, physiotherapist (PT), occupational therapist (OT), psychologist, speech and language pathologist (SLP), and dietitians. Module will be written in both English and Bahasa Malaysia. The module design phase consist of:

- - - 1. Determining the study objective
      2. Overall module content
      3. Activities of each component
         1. Medical and nursing management
         2. Rehabilitation management – PT, OT, SLP, psychologist and dietitians
      4. Detailed description and instruction of each activity
      5. Flow of the module contents

## Instrument designing

Variables identified for this study involves functions, mobility and QoL of persons with PD while for caregivers involves knowledge of PD, burden of caregiving and QoL. There are four instruments which does not require validation as its psychometric properties are already established, namely:

- - - 1. Movement Disorder Society-Unified Parkinson’s Disease rating scale (MDS-UPDRS) and Timed Up and Go (TUG) test which measures functionality and mobility of persons with PD respectively.
      2. EuroQoL-5 Dimensions (EQ-5D) and Malay version of Zarith Burden Interview (ZBI) measuring the caregiver’s QoL evaluating and burden of caregiving respectively.

However, translation and validation is compulsory for questionnaire measuring knowledge of PD among family caregivers using questionnaire developed by Moore and Knowles, (2006). A copy of approval email to use the questionnaire of Moore and Knowles (2006) is attached in appendix 8. The steps involved for the translation of the knowledge of PD among caregivers instrument is shown in Figure 4 based on a study by Sousa and Rojjanasrirat (2011). While validation of Bahasa Malaysia version of EQ-5D among persons with PD in Malaysia will be conducted by performing full psychometric testing. Language and subject experts in the instrument design phase will be recruited via purposive sampling from UKM. Approval is also obtained to use the Malay version of ZBI as attached in appendix 8.

Identify one language and subject expert (n=2) for English to Bahasa Malaysia translation

Comparison of the two translated versions of the instrument

Identify one language and subject expert (n=2) for Bahasa Malaysia to English translation

Blind back-translation of the preliminary initial translated version of the instrument

Comparison of the two back-translated versions of the instrument

Pilot testing of the pre-final version of the instrument in the target language

Preliminary psychometric testing of the pre-final version of the translated instrument

Full psychometric testing of the pre-final version of the translated instrument

in a sample of the target population, caregivers of persons with PD

Figure 4 Flow chart of knowledge of PD among caregivers instrument design

## Module development

Procedure 1: Designed module will be discussed with the team of experts mentioned earlier to approve for content and storyboard to commence development in dual language. Pre- developed module will be submitted to the illustrator for better quality development.

Procedure 2: Validation of the developed module through percentage calculation method (PCM) and content validity index (CVI)

- - - 1. Recruitment of experts meeting the eligibility criteria as below via purposive sampling from UKMMC and UKM:
         1. Inclusion criteria: Minimum Masters or PhD in neurology or geriatric care with at least three years of clinical experience managing PD persons and caregivers.
         2. Exclusion criteria: Experts who are not able to provide informed consent.
      2. A total of 7 experts namely neurologist, nurses, OT, PT, SLP, psychologist and dietitians will be recruited based on the eligibility criteria to answer Module Validity Testing Questionnaire (Russell, 1974). The questionnaire is based on 5 point Likert scale with score 1 (highly agree) and score 5 (totally disagree). Five items will be analyzed;
         1. Suitability of module content to family caregiver and persons with PD
         2. Successful implementation of the module content
         3. Module content is suitable with allocated time
         4. Module content may provide positive impact
         5. Module content may provide desired results among family caregiver and persons with PD
      3. Percentage calculation method to determine the level of module content validity. This will be obtained by dividing the number of scores filled by the experts to the actual score and multiplied by 100. Acceptable value will be 70% and above (Tuckman and Waheed, 1981 & Sidek and Jamaluddin, 2005).
      4. Content validity index will be calculated as follows;
         1. Divide the 5 point ordinal Likert scale into two categories; score 0, 1 and 2 (agreed) = give score 0 and above score 2 is disagreed = give score 1.
         2. Compute each items of the five criteria from based on the two categories by each experts
         3. CVI of each items are calculated by dividing the sum of the evaluators agreed with sum of evaluator as shown in example of the table below.

Procedure 3: Reliability analysis. Analysis of Cronbach’s alpha coefficient will be calculated. (Sidek & Jamaluddin, 2005).

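### The 70% content-validity rule runs against its own rating scale: agreement is scored low, yet a high percentage is required

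*Protocol*

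**What the plan says.** Everything needed stands in the Protocol, Phase II, Module development, Procedure 2.

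- **Raters:** "A total of 7 experts namely neurologist, nurses, OT, PT, SLP, psychologist and dietitians will be recruited".
- **Items:** "Five items will be analyzed".
- **Scale:** "The questionnaire is based on 5 point Likert scale with score 1 (highly agree) and score 5 (totally disagree"). Low ratings therefore mean endorsement.
- **Percentage calculation method (PCM):** "This will be obtained by dividing the number of scores filled by the experts to the actual score and multiplied by 100". The denominator is not defined further.
- **Acceptance:** "Acceptable value will be 70% and above".
- **CVI grouping:** "score 0, 1 and 2 (agreed) = give score 0 and above score 2 is disagreed = give score 1".
- **CVI formula:** "CVI of each items are calculated by dividing the sum of the evaluators agreed with sum of evaluator".

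The section does not say that ratings are reversed before the PCM is computed.

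**The concern.** Three rules are fixed together: agreement is scored low, the PCM rises with the score, and a high PCM is required. They cannot all serve the stated purpose. Each additional expert who agrees strongly pulls the percentage away from the acceptance value.

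This is not one misprinted label. The CVI grouping also treats ratings up to 2 as agreement and higher ratings as disagreement, so the low-means-agree direction appears twice. Swapping the anchor wording alone would repair the PCM and break the CVI cut.

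Validating the module is part of specific objective 3, and Figure 1 lists content validation ahead of the pilot trial. The 70% figure is the only numerical acceptance value in the visible text of Procedures 2 and 3. If the conflict is noticed only once the ratings are in, the team will choose a recoding with the answers in view. A threshold set in advance is meant to prevent that.

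**Working it through.** The plan has no derived figure to reproduce here, because 70% is a decision threshold. The check is whether the rule gives the right answer for ratings whose meaning is plain.

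**Inputs** (all from Procedure 2): 7 experts, 5 items, ratings 1 to 5 with 1 the strongest agreement, acceptance at 70% or more. Assumption: the 'actual score' is the maximum obtainable total, 7 × 5 × 5 = 175.

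**PCM as written.** PCM = 100 × (sum of ratings) / 175. If every rating equals *s*, the sum is 35*s* and PCM = 100 × *s*/5.

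| Every expert gives | Sum | PCM as written | 70% rule | CVI as defined |
| --- | --- | --- | --- | --- |
| 1 (strongest agreement) | 35 | 20% | fail | 7/7 = 1.0 |
| 2 | 70 | 40% | fail | 1.0 |
| 3 | 105 | 60% | fail | 0 |
| 4 | 140 | 80% | pass | 0 |
| 5 (strongest disagreement) | 175 | 100% | pass | 0 |

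**Where the threshold falls.** 0.70 × 175 = 122.5, and 122.5 / 35 = 3.5. The mean rating must be at least 3.5, on the disagree side of the midpoint. If every rating lies in the protocol's own agreed range (2 or below), PCM cannot exceed 2/5 = 40%.

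**A mixed panel.** Six experts give 1 throughout and one gives 5 throughout: (6 × 5 × 1 + 5 × 5) / 175 = 55/175 = 31.4%, a fail.

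**Other readings of the denominator.**

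- *Per item.* The maximum is 7 × 5 = 35 and the sum is 7*s*, so PCM is again *s*/5. The inversion is the same.
- *Rescaled to the range, (s − 1)/4.* Ratings 1 to 5 give 0%, 25%, 50%, 75% and 100%. Still inverted.
- *Ideal total, all experts giving 1: 7 × 5 × 1 = 35.* PCM runs from 35/35 = 100% to 175/35 = 500%. The rule can never reject. (This 35 is the lowest total over all five items and differs in meaning from the per-item maximum of 35.)

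**With reverse-scoring.** Replace each rating by 6 − rating and keep 175 as denominator. Unanimous ratings of 1 to 5 then give 100%, 80%, 60%, 40% and 20%, so 1 and 2 pass and 3 to 5 fail. The mixed panel gives (6 × 5 × 5 + 5 × 1) / 175 = 155/175 = 88.6%, a pass. The 70% rule now works in the intended direction.

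**The case against.** **The denominator is undefined.** The inversion in the table depends on reading it as the maximum total, and the sources cited for the method are not at hand. This stands as a limit on the exact percentages. It does not save the rule, since every reading tried leaves it inverted or unable to reject.

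**The CVI may look inverted too.** A reader might infer this from the codes, because agreement is coded 0 and disagreement 1, so summing the codes would count those who disagree. The text does not sum the codes. Its formula puts the experts who agreed over all experts, which gives 1.0 for unanimous endorsement. The codes merely run against that formula. The worked example the section points to is not in the text available, so nothing should be inferred from it. The rating of 0 in the grouping is a harmless slip, since nobody can give 0 on a 1 to 5 scale.

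**The 70% value may look like a go/no-go gate for the trial.** A reader might infer this from the order of the phases. No section makes the pilot or Phase III conditional on it, and none says what follows a lower value. Procedure 1 also seeks expert approval of the content, and Procedures 2 and 3 add the CVI and Cronbach's alpha. A module the experts rejected would show a CVI near 0 beside a PCM of 80% to 100%, and that contradiction would be visible.

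**The fault is recoverable.** The anchors are explicit, so ratings can be reversed after collection without loss of data. That is true and lowers the severity. It does not make the stated rule correct.

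**Conclusion.** The PCM acceptance rule is wrong as written. With the maximum total of 175 as denominator, unanimous strongest agreement scores 20% and fails, while unanimous strongest disagreement scores 100% and passes. The 70% line sits at a mean rating of 3.5. With the ideal total of 35 as denominator, the rule accepts everything. The CVI runs in the right direction, so on the first reading the two measures would disagree about the same ratings: CVI 1.0 beside PCM 20% for a fully endorsed module.

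The percentages rest on reading the denominator as the maximum. The conclusion that the rule cannot do its job holds under each reading examined. The effect is confined to the Phase II content-validity criterion under specific objective 3. The randomised trial's sample size and analysis are untouched. Moderate severity.

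**What to change.** Before the questionnaire goes to the experts, amend Procedure 2 as follows.

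1. State that each rating is replaced by 6 − rating before the PCM is computed.
2. Define the denominator as the maximum obtainable total: 175 overall, or 35 per item.

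Alternatively, reverse the anchors so that 5 is the strongest agreement, and in the same edit move the CVI agreed range to 4–5. Changing the anchors without moving that cut would invert the CVI.

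For tidiness, code CVI agreement as 1 and disagreement as 0 to match the formula, and delete the rating of 0 from the grouping.

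The cost is a few lines of wording. No additional experts, items or data are needed.

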## Formative evaluation: Pilot RCT

1. **Study design**

Quantitative approach using experimental design, a pilot RCT.

## Target Population

The target population in this study are PD patients of stage I and II, and their family caregivers.

## Eligibility criteria Inclusion criteria:

- 1. PD patients

1. 50-75 years old
2. Stage I and II of Parkinson’s disease based on HY scale
3. Availability of family caregivers.
   1. Family caregivers
      1. Main caregiver who lives with the PD patient

## Exclusion criteria:

1. PD patients
2. Impaired physical function due to other conditions such as a recent fracture within the past 6 months, severe arthritis or other neurological disease such as peripheral neuropathy.
3. Have medical illness limiting participation in exercise, such as unstable angina and uncontrolled hypertension.
4. Family caregiver:
   1. Providing part-time caregiving due to availability of maid/helper
   2. Presence of clinically diagnosed depression with a cutoff point of ≥16 in CES-D.
   3. Presence of mild cognitive impairment or dementia with a cutoff point of ≤26 in MoCA.

## Sampling Frame

Main sampling frame for this study phase is all persons with PD registered with the MPDA or PD patients referred to the Medical Rehabilitation Services Department of UKMMC since January 2021 and their main family-caregiver. MPDA registry and patient’s registry maintained by the neurology rehabilitation unit of the department will be accessed to identify PD patients.

